### Data analysis plan

All analyses will follow an intention-to-treat principle with participant data within clusters analyzed according to the cluster’s randomized crossover time. All quantitative analyses will utilize a type I error rate of *p* < 0.05. Multiple imputation will be used for missing secondary psychological outcomes, with separate imputations conducted by study phase and clinic, incorporating demographic variables to ensure the accuracy of imputed values under the assumption of missing at random. Analyses will be conducted using STATA version 14.2, R statistical software, or the Statistical Package for the Social Sciences (SPSS, version 31.0).

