#### Aim 1: Impact of FAMES on primary and secondary outcomes

##### Quantitative data analysis

Statistical analyses for primary engagement outcomes will use Generalized Linear Mixed Models (GLMM) to compare engagement rates between the control (ACC) and intervention (FAMES), with a random effect for cluster (site), a fixed effect for each phase (ACC and FAMES), and a fixed effect for implementation wave to control potential time-related confounding [80, 81]. GLMM will also be used to assess change scores on secondary outcomes for family member and client participants from baseline to 3 months. Restricted maximum likelihood estimation with Kenward-Roger standard error and degrees of freedom correction to accommodate for our relatively small number of clusters will be used. Supplemental analyses will assess the likelihood of including relevant individual and program covariates (e.g., age, biological sex, race, and others) in models if significant differences among covariates occur between ACC and FAMES samples. Analysis of the secondary outcomes collected only from FAMES participants at follow-up will employ GLMMs to compare baseline to 3-month to follow-up inventory scores as a random effect repeated measures factor. Fixed effect covariates (e.g., age, biological sex, race, and others) will be included in these models as appropriate. A Bonferroni correction will be applied to primary engagement outcomes (first session attendance and total attendance per family and client) to control for multiple testing.

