#### Aim 2: Assess whether target mechanisms mediate FAMES engagement

##### Quantitative data analysis

To examine whether potential mechanisms (connectedness, self-efficacy, and motivation) mediate engagement in FAMES, hierarchical linear regression (HLR) will be used, with predictor variables entered in sequential steps. Demographic variables (age, gender, biological sex, race, ethnicity, years of education, employment status, marital status, clinic), will be entered in Block 1, followed by changes in mediator variables in Block 2. The unique contribution of each mediator will be assessed using changes in adjusted R2, and only significant predictors will be retained in the final models. Regression assumptions will be evaluated using variance inflation factors (multicollinearity) and Durbin-Watson statistics (independence of errors). To explore potential nonlinearity, alternative specifications such as interaction terms or polynomial transformations may be tested.

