#### Aim 3: Explore implementation outcomes using mixed methods

##### Quantitative data analysis

All implementation outcomes will be analyzed using GLMM to account for clinic- and provider-level clustering and repeated measurements over time. The models will include random effects for sites and providers and fixed effects for time (such as monthly changes in reach and adoption). Since provider characteristics such as gender, race, and education may influence implementation, they will be included in models if they improve accuracy, as assessed by Akaike Information Criterion (AIC) and Bayesian Information Criterion (BIC). Because some providers may drop out or miss assessments, multiple imputation (MI) will be used to estimate missing data, ensuring unbiased results.

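### Retaining only significant predictors in the Aim 2 models overstates the mechanisms that survive (about 1.1 to 1.5 times at the planned effect) and, as worded, can remove clinic

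*Protocol article*

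**What the plan says.** The Aim 2 quantitative analysis section of the protocol article describes a regression in blocks: "hierarchical linear regression (HLR) will be used, with predictor variables entered in sequential steps". The first block is fixed in advance: "Demographic variables (age, gender, biological sex, race, ethnicity, years of education, employment status, marital status, clinic), will be entered in Block 1". Changes in connectedness, self-efficacy and motivation form Block 2. Each mediator's contribution is judged by the change in adjusted R², and the same sentence ends by saying that "only significant predictors will be retained in the final models". No term is exempted from this rule.

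The Aim 2 section names no random site effect and no cluster-robust standard error. Independence is to be examined with "Durbin-Watson statistics (independence of errors"), which is a diagnostic and adjusts nothing. The other aims do model site: Aim 1 "with a random effect for cluster (site"), and for Aim 3 "The models will include random effects for sites and providers".

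The Power analysis section sizes Aim 2 on the whole three-mediator block, with 225 families, an R² change of 0.10 and alpha 0.025. It does not size a model reduced by p-value.

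**The concern.** Aim 2 asks which of three theory-driven mechanisms are related to engagement in FAMES. If terms are dropped for p ≥ 0.05 and the model is refitted on the same families, two things happen. First, a mechanism is kept only when its estimate came out large enough, so the estimates that survive are too large on average. Second, when mechanisms are positively correlated, a survivor absorbs part of the effect of the one removed, so its coefficient no longer describes what the three-mechanism model was set up to describe. The plan anticipates correlated predictors, since it checks variance inflation factors.

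A secondary problem is that the section uses the word predictor for variables in both blocks, and clinic is in Block 1. Taken literally, a non-significant clinic term goes too. The model then treats families nested in nine clinics as independent.

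**Working it through.** **Inputs from the protocol.** N = 225; 9 sites (25 families per site if equal); Block 1 R² = 0.10 with 7 predictors; Block 2 R² change = 0.10 with 3 predictors at alpha 0.025; general alpha 0.05; ICC 0.01, stated for Aim 1 only. The protocol gives no correlation among mechanisms, no split of the R² change, and no ICC for FAMES engagement or the mechanisms. Values for these are assumptions.

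**Step 1: the plan's own power.** Noncentral F with λ = f²·N.
- Block 1: f² = 0.10/0.90, λ = 25.0, df 7 and 217. Power is 96.9% (stated 98%).
- Block 2: f² = 0.10/(1 − 0.20) = 0.125, λ = 28.1, df 3 and 214. Power is 99.3% (stated 99%).

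The stated figures are reproduced to within about one point.

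**Step 2: what the planned effect means per mechanism.** For three standardized mechanisms with equal effects β and common correlation ρ, the R² change is β²(3 + 6ρ).
- ρ = 0: β = √(0.10/3) = 0.183.
- ρ = 0.3: β = √(0.10/4.8) = 0.144.
- β = 0.10 with ρ = 0.3 gives an R² change of 4.8 × 0.01 = 0.048, about half the plan.
- β = 0.05 with ρ = 0.3 gives 4.8 × 0.0025 = 0.012.

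**Step 3: simulate the rule.** Fit the full model, drop terms with p ≥ 0.05, refit, and score the survivors against the full-model coefficient (4,000 to 6,000 data sets per case).

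| Case | R² change | Mean estimate ÷ true | 95% CI coverage |
|---|---|---|---|
| Uncorrelated, planned effect | 0.10 | about 1.1 | about 97% |
| ρ = 0.3, planned effect | 0.10 | about 1.5 | about 87% |
| ρ = 0.3, weaker than planned | 0.048 | about 2.1 | about 71% |
| ρ = 0.3, much weaker | 0.012 | about 3.5 | 45–49% |

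Runs differ by a few points with the residual variance assumed; the second row came out between 1.4 and 1.5. Coverage in the unpruned model was about 95% throughout.

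**Step 4: clinic.** Its F test has 8 and 225 − 9 = 216 df, with critical value 1.98. With 25 families per site, the chance of significance is P(F > 1.98/[1 + 25·ICC/(1 − ICC)]).
- ICC 0.01: divisor 1.25, so 13%. Clinic is dropped in about 87% of samples.
- ICC 0.05: divisor 2.32, so about 55%. Clinic is dropped in about 45%.

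Type I error for a mechanism with no effect, by simulation (5,000 data sets):

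| Outcome ICC / mechanism ICC | Without clinic | With clinic |
|---|---|---|
| 0.01 / 0.01 | 5.1% | 5.3% |
| 0.05 / 0.05 | 5.9% | 4.9% |
| 0.10 / 0.10 | 7.7% | 5.1% |
| 0.10 / 0.20 | 10.2% | 4.8% |

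**Step 5: what pruning saves.** Keeping everything means 8 other Block 1 variables counted as one term each, 8 clinic dummies and 3 change scores, 19 terms in all. Residual df are 225 − 1 − 19 = 205, and Block 2 power at alpha 0.025 is 99.3%, the same as with 10 terms.

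**The case against.** Several counter-arguments carry weight.

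- **The size depends on the scenario.** At the planned R² change with uncorrelated mechanisms, the bias is about 10% and coverage is nominal or better. A reader might infer that effects will be doubled or tripled; that requires mechanisms well below the planning value. This stands.
- **Intervals are not too narrow in general.** At the planned effect with correlation 0.3, the refitted interval covers the reduced model's own coefficient about 97% of the time. The 87% arises because that coefficient is a different quantity, on average about 1.27 times the full-model one. This stands, but the full-model coefficient is the one Aim 2 is about.
- **Refitting is not the only source.** Mechanisms significant in the unpruned model are already overstated about 1.3 times at the planned effect with correlation 0.3. Reporting the full model helps because all three coefficients are shown, not because the significant ones become unbiased.
- **The rule may be meant for mediators only.** Its sentence opens with the contribution of each mediator, so this reading is possible. The text does not limit it so, and selection among mechanisms would remain.
- **The block-level results may also be reported.** The protocol does not say they will be withheld, and the joint Block 2 test is not altered by later pruning. That is fair, but the final model is still defined as the pruned one.

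**Conclusion.** The point holds. As written, the rule selects among three prespecified mechanisms by p-value and estimates them on the same 225 families, and nothing else in the protocol corrects for it. At the planned effect, split equally, the overstatement is about 1.1 times (uncorrelated) to 1.5 times (correlation 0.3, assumed), with coverage of the full-model coefficient about 97% and 87%.

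The loss of clinic is secondary. It follows from the literal wording, but its effect on type I error is negligible at 0.01, the only ICC the protocol states, and visible only from about 0.05 upwards. A reader might infer that Aim 2 would be invalid for lack of site control; the documents give no ICC that would support this. Nor is the Aim 1 comparison affected, since it has its own random site effect.

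**What to change.** Delete the retention rule and state instead that:

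- the Aim 2 result is the full prespecified model, with all Block 1 covariates and all three change scores;
- clinic stays in the model whatever its p-value;
- Block 2 is tested jointly at the 0.025 level used in the Power analysis section;
- each mechanism's coefficient is reported with its 95% CI, significant or not;
- any reduced model is labelled exploratory.

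The cost is a sentence or two of analysis text and a few degrees of freedom. The change can be made before the FAMES data are analysed, since recruitment is expected to run to October 2029.

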#### Aim 3: Explore implementation outcomes using mixed methods

##### Quantitative data analysis

All implementation outcomes will be analyzed using GLMM to account for clinic- and provider-level clustering and repeated measurements over time. The models will include random effects for sites and providers and fixed effects for time (such as monthly changes in reach and adoption). Since provider characteristics such as gender, race, and education may influence implementation, they will be included in models if they improve accuracy, as assessed by Akaike Information Criterion (AIC) and Bayesian Information Criterion (BIC). Because some providers may drop out or miss assessments, multiple imputation (MI) will be used to estimate missing data, ensuring unbiased results.

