### Study sites

Nine CSC programs geographically distributed throughout the USA will serve as study sites. The geographical location of sites represents both rural and urban communities, hospital-based and community-based programs, and has a combined ethnoracially diverse set of families. CSC programs are generally comprised of a program director, family education and support specialist, peer support specialist, case manager, education and employment specialist, and a medical prescriber. Nine part-time family peers, with lived experience of having a loved one who has experienced psychosis, will be hired by each CSC at least three months prior to the pre-implementation phase. Across the nine CSC sites, the following team roles will be consented to participate in study activities: Program directors/supervisors (*n* = 4), family education and support providers (*n* = 4), program director/family education and support provider (*n* = 4), and family peers (*n* = 9).

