**Fig. 2 Fig2:**

The modified stepped-wedge randomized trial across three waves. CSC, Coordinated Specialty Care; ACC, Attention Control Condition; FAMES, Family Motivational Engagement Strategy; CFI, Cultural Formulation Interview

After site randomization, each CSC program will be allotted 18 months to recruit participant dyads to receive the ACC during the control phase, after which sites will participate in a three-month pre-implementation phase to commence training of family peers, program directors, and family education and support providers, followed by a 30-month active implementation phase to recruit a new cohort of participant dyads to receive FAMES (Fig. 2).

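### The Aim 3 model names no site-specific time trend, so its test of monthly change in reach or adoption is anti-conservative if the nine sites drift differently

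*Protocol article*

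**What the plan says.** The Aim 3 quantitative section of the protocol article applies one model family throughout: "All implementation outcomes will be analyzed using GLMM to account for clinic- and provider-level clustering and repeated measurements over time". It then names the terms: "The models will include random effects for sites and providers and fixed effects for time (such as monthly changes in reach and adoption"). No site-by-time term or random slope is mentioned.

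Under Study sites: "Nine CSC programs geographically distributed throughout the USA will serve as study sites". The staff listed there are 4 program directors or supervisors, 4 family education and support providers, a further group in both roles, "program director/family education and support provider (*n* = 4"), "and family peers (*n* = 9"). The active phase is long: "followed by a 30-month active implementation phase to recruit a new cohort of participant dyads to receive FAMES".

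Table 2 has reach and adoption measured monthly. Reach is the share of service users identified at intake who enrol in FAMES. Adoption is the share of family psychoeducation sessions that use FAMES information, taken from a provider survey. The Data analysis plan sets a 5% type I error rate for all quantitative analyses. The Aim 1 section says that a "degrees of freedom correction to accommodate for our relatively small number of clusters will be used"; the Aim 3 section does not repeat this.

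**The concern.** A random intercept lets a site sit above or below the average. It does not let a site rise or fall at its own rate. With time entered only as a fixed effect, the model treats monthly data from nine sites as repeated looks at one shared trend, and the precision of that trend grows with the number of intakes or sessions. If sites really follow different trends, the evidence about the average trend comes from nine slopes, and collecting more sessions per site does not change that.

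Differing trends are plausible here. The sites are rural and urban, hospital-based and community-based. The protocol expects interviews to inform modifications during implementation, and its qualitative analysis arranges codes in time order by site. At stake is a statement that reach or adoption changed during FAMES delivery when the sites merely moved in different directions.

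**Working it through.** **The plan's own Aim 3 figure.** The only Aim 3 power figure is for knowledge: n = 20, standardized difference 0.60, correlation 0.50, one-sided alpha 0.05, power 83%. For a paired t-test, dz = 0.60/√(2(1 − 0.50)) = 0.60, the noncentrality is 0.60 × √20 = 2.68, and power on 19 df is 82.7%. The figure reproduces, but it says nothing about trends. No power or sample size is given for change in reach or adoption.

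**Inputs from the protocol article.** Nine sites, 30 months, alpha 0.05, 225 FAMES enrolments.

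**Assumptions, not in the article.** The average trend is zero and the level is 50%. The site-intercept SD is 0.5 logits. The SD s of the site-specific change over 30 months is 0 to 1.0 logits. At a 50% level, a site one SD above average would move from about 47% to 53% (s = 0.25), 44% to 56% (s = 0.5) or 38% to 62% (s = 1.0).

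**Counts per site-month (m).** For reach, 225/(9 × 30) = 0.83 enrolments per site-month; at 50% reach this is 0.83/0.50 = 1.67 intakes. For adoption the article gives no session count, so m = 5 is taken as a possible value.

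**Approximate formula.** Scale time to run over one unit across the 30 months. The sum of squared centred times is then 2.67 per site. With p(1 − p) averaging 0.236, the information on one site's slope is about 0.236 × 2.67 × m = m/1.6. Ignoring slope variation understates the variance of the common trend by the factor V = 1 + s²m/1.6. The true rejection rate of a nominal 5% test is 2[1 − Φ(1.96/√V)].

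**Simulation.** 2,000 runs per cell. The common-trend model is logistic with site intercepts (as fixed terms standing in for the random intercept) and one slope.

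| m | s | V | Formula | Simulated, common trend | Simulated, nine-slope t-test (8 df) |
|---|---|---|---|---|---|
| 1.67 | 0 | 1.00 | 5.0% | 4.7% | 4.6% |
| 1.67 | 0.25 | 1.07 | 5.8% | 5.2% | 4.5% |
| 1.67 | 0.5 | 1.26 | 8.1% | 8.5% | 4.5% |
| 1.67 | 1.0 | 2.04 | 17.0% | 15.8% | 4.4% |
| 5 | 0 | 1.00 | 5.0% | 4.6% | 4.1% |
| 5 | 0.25 | 1.20 | 7.3% | 7.7% | 4.8% |
| 5 | 0.5 | 1.78 | 14.2% | 13.5% | 5.1% |
| 5 | 1.0 | 4.13 | 33.5% | 30.7% | 5.7% |

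**Sensitivity to the reach level.** With enrolments fixed at 225, lower reach means more intakes and more information. At 15% reach, a simulation of 1,500 runs gave 5.1%, 7.6%, 11.6% and 27.4% for s = 0, 0.25, 0.5 and 1.0.

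**Role of the provider term.** In a Gaussian version (20,000 runs, s = 1.0 residual SD), one provider per site gave 29.0% with and without the provider effect. Two providers per site gave 41.4% without it and 42.3% with it. The provider term does not drive the inflation.

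**Whether the provider term can be estimated.** There are 9 family peers for nine sites, and 4 + 4 = 8 people who hold the family education role. Reach is a site-level proportion with no natural provider level. All staff together are 4 + 4 + 4 + 9 = 21, about 2.3 per site, so knowledge and acceptability can support both effects.

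**The case against.** Five objections deserve an answer.

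- **The text does not exclude slopes.** Random effects for sites could include slopes, and a fuller document may say so. This stands in part: a reader might infer that the plan forces one trend on all sites, and the wording does not go that far. But the section does name its random terms and gives monthly change in reach and adoption as its example, so the plain reading is intercepts with a common trend.
- **The harm is conditional.** This stands. With identical site trends the error is nominal, and with mild drift at reach-like counts it is close to 5%. A reader might infer that a false trend will be reported; the article supports only that it can be.
- **Large inflation does not fit reach at a 50% level.** This stands. Counts of 8 or 16 intakes per site-month would imply 1,080 or 2,160 enrolments (9 × 30 × 8 or 16, × 0.50) against 225 planned.
- **Provider and site may not coincide.** Staff are given as role totals, not by site. Several staff at a site may answer the provider survey, and staff may be replaced over 30 months. This stands: a reader might infer that the provider effect duplicates the site throughout, or that it causes the false positives. The role totals do not establish the first, and the calculations contradict the second.
- **Aim 3 is exploratory and powers no trend.** This lowers the importance but does not correct the standard error.

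The unrepeated small-sample correction is not a separate fault: in an intercept-only model it would not supply the missing slope variance.

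**Conclusion.** The point holds as a conditional weakness in the stated model. As written, the Aim 3 trend test makes no allowance for sites changing at different rates. For a slope SD of 0.25–1.0 logits and a 50% level, the false-positive rate is about 5–16% for reach and about 8–31% at 5 observations per site-month. A test that uses the spread of the nine site slopes stays between 4.1% and 5.7% in the table's scenarios. The slope SD, the level and the adoption count are assumptions, and the calculation treats time as linear. It does not cover competence, which is measured at only four time points. The provider term is a lesser matter of whether two variances can be separated. The Aim 1 comparison is untouched. This is a cheap improvement to an exploratory aim and does not threaten the trial's main conclusion.

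**What to change.** In the Aim 3 quantitative section, state that for outcomes followed monthly (reach and adoption) the model includes a random site intercept and a random site slope for time, and that the time effect is tested with about 8 degrees of freedom. A t-test on the mean of the nine site slopes is an acceptable alternative and simpler to fit. Separately, state that the provider random effect is kept only where a site has more than one provider contributing data, for example for knowledge and acceptability, or where staff are replaced.

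The change is to analysis wording only. It gives wider intervals and some loss of power when sites do share one trend: a test with 89% power on the normal scale (noncentrality 1.96 + 1.23 = 3.19) has about 80% power on 8 df.

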##### Longitudinal qualitative data analysis

A conventional content analysis approach will be used to initially code transcripts from CSC team members. Three members of the research team will independently read and analyze 20% of transcripts, developing codes and themes that come from the data prior to reaching consensus. To guard against biases, an audit trail documenting analytical decisions will be created and peer debriefing meetings will be held. Meeting discussions and notes will be used to develop a final code book. The remaining transcripts will be coded by trained research staff. ATLAS.ti software will be used to assist with analysis [82]. A trajectory analysis approach will be used to understand experiences over time, when the same cohort can be maintained that can then be compared [83, 84]. Codes will be organized into time-ordered sequential matrices per site. Codes deriving from transcripts will be entered into a series of matrices organized by themes and time points by sites and across sites.

